## Abstract

**Introduction:**

Enteral nutrition (EN) is the preferred route of medical nutrition therapy for critically ill patients. However, enteral feeding intolerance remains a frequent challenge when implementing EN. Pectin, a water-soluble dietary fiber, has been shown to reduce diarrhea and improve feeding tolerance, but existing evidence remains inconsistent. The PROMOTE trial aims to evaluate whether EN supplemented with pectin, compared to usual care, improves EN delivery in critically ill patients.

**Methods:**

This is a multicenter, open-label, randomized, parallel-controlled trial, conducted in 10 centers across China. Newly admitted adult critically ill patients who received invasive mechanical ventilation for less than 72 h and had an indication for EN via gastric access will be enrolled. In addition to standard care, patients assigned to the intervention group will receive EN supplemented with 90 g of pectin per 500 mL of EN solution. The study intervention will be discontinued 7 days after randomization, upon discharge from the study site, upon death, or upon cessation of gastric feeding, whichever occurs first. The primary outcome is the ratio of EN energy intake to the prescribed target energy on Day 5 after randomization. Secondary outcomes include daily energy and protein intake, the incidence of enteral feeding intolerance, duration of ICU stay, duration of mechanical ventilation, duration of hospital stay, 28-day mortality, ICU-free, hospital-free and ventilation-free days to 28 days.

**Discussion:**

This study investigates whether pectin-supplemented EN enhances gastric feeding tolerance and clinical outcomes in critically ill patients. The finding will provide evidence on pectin’s efficacy in optimizing EN delivery and guide early gastric feeding strategies in critical care.

**Clinical trial registration:**

https://www.chictr.org.cn, identifier ChiCTR2300078477.

## Introduction

1

Early initiation of enteral nutrition (EN) is critical for critically ill patients. Both ASPEN and ESPEN guidelines recommend starting EN with 48 h rather than delaying EN or initiating early parenteral nutrition (PN) (1, 2). Gastric delivery remains the standard initial route. However, EN frequently fails due to feeding intolerance, which affects approximately 20%–30% of critically ill patients and presents with elevated gastric residuals, nausea, vomiting, abdominal distension, or diarrhea (3, 4). Furthermore, this intolerance is associated with serious risks such as aspiration, inhalation pneumonia, and potentially fatal outcomes (5).

Current strategies for managing feeding intolerance are limited. Initial measures include prokinetic agents (e.g., erythromycin, metoclopramide) and formula adjustments, followed by post-pyloric feeding if needed (6, 7). If intolerance persists despite these interventions, PN is initiated. However, this stepwise approach is not always effective and can be time-consuming, potentially depriving patients of adequate EN and its associated benefits (7, 8). Feeding intolerance may be directly related to EN itself (9). For instance, the high osmolarity of EN formulations can contribute to diarrhea (10), while the low viscosity and high infusion rate may increase the risk of gastroesophageal reflux and subsequent aspiration (11).

Pectin, a gelatinous substance derived from the cell walls of fruits and plants, is a major component of water-soluble dietary fiber and possesses multiple biological activities. In the acidic gastric environment, pectin can interact with calcium ions (Ca^2+^) to form a semi-solid gel (12, 13). Increasing the viscosity of EN with pectin may therefore reduce diarrhea and reflux aspiration risk (14). A systematic review and meta-analysis showed that pectin-supplemented EN was associated with reduced diarrhea, fewer infectious complications, and a shorter length of stay (15). Notably, its effect was evident in patients not receiving proton pump inhibitors (PPIs) but absent in those on PPIs (16), likely because conventional pectin requires an acidic environment to gel. Low-esterified pectin, however, can form a stable hydrogel even under low-acid conditions, via a pH-independent Ca^2+^-mediated gelation mechanism (17), thereby increasing intragastric content cohesiveness and reducing retrograde flow and reflux-driven interruptions. This distinguishes our intervention from generic fiber supplementation and broadens its applicability to the general critically ill population.

Although pectin supplementation appears promising in reducing feeding intolerance and improving clinical outcomes, most existing evidence comes from observational studies or small, single-center randomized controlled trials (RCTs). To address this gap, we plan to conduct a multicenter RCT (PROMOTE trial). Our hypothesis is that EN supplemented with low-esterified pectin, a physiochemically more robust form of pectin, will improve feeding tolerance and enable greater total energy delivery compared with usual care in critically ill adults.

## Methods and analysis

2

### Study design, setting, and population

2.1

PROMOTE is a multicenter, open-label, randomized, parallel-controlled trial conducted by the Chinese Critical Care Nutrition Trials Group (CCCNTG). The trial will enroll 212 critically ill adult patients from ten intensive care units (ICUs) across China. Trial oversight will be provided by a Trial Management Committee (TMC), comprising the principal investigators from each participating center and key members of CCCNTG, which will be responsible for the overall conduct and coordination of the study. Recruitment started in February 2024 with competition for enrollment expected in 2026. The trial protocol was developed according to the Standard Protocol Items: Recommendations for Interventional Trials (SPIRIT) statement (18).

Patients aged ≥ 18 years and within 24 h of their index ICU admission will be screened for eligibility. Those requiring invasive mechanical ventilation and, therefore, unable to take oral nutrition, necessitating artificial nutritional support, will be eligible for inclusion. The complete inclusion and exclusion criteria are listed below:

#### Inclusion criteria

2.1.1

1. Aged ≥ 18 years old;

2. Admitted to ICU < 24 h;

3. Receive invasive mechanical ventilation < 72 h, and the expected duration of continued treatment > 48 h;

4. Do not expect to feed orally for more than 3 days and plan to receive gastric feeding;

5. No operation plan within a week;

6. Informed consent form obtained from the patient or next of kin.

#### Exclusion criteria

2.1.2

1. Patients who had started EN before admission to ICU;

2. Patients who have had a nasointestinal tube placed and are scheduled to receive enteral feeding;

3. Patients with contraindications to EN;

4. Patients receiving palliative care or expected to die within 48 h;

5. Patients known to be pregnant or currently breastfeeding;

6. The treating clinician believes a specific high-calorie (or low-calorie) nutritional formula is indicated.

### Randomization and blinding

2.2

The randomization sequence will be generated by an independent statistician using SAS Version 9.4 with a fixed block size of 4, ensuring allocation in a 1:1 ratio. Randomization will be stratified by study site. Allocation concealment will be ensured through a secure, encrypted, password-protected central web-based randomization system.^1^

Blinding of participants and treating clinicians was not feasible because pectin supplementation changes the handling and administration characteristics of the enteral formula, making it distinguishable from standard care during routine clinical practice. No placebo will be provided to the control group. Nonetheless, outcome assessors and data analysts will remain blinded to group assignments to minimize assessment and analytic bias.

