Diarrhea represents one of the most common manifestations of EN intolerance in the critically ill, with reported rates of 10%–70% among ICU patients receiving EN, reflecting genuine variability across populations, feeding routes, and definitions (9, 15). Given the multiple mechanisms by which pectin may attenuate diarrhea, including increased stool consistency, modulation of colonic transit, and enhancement of intestinal barrier integrity, diarrhea incidence is therefore included as a pre-specified secondary outcome to provide exploratory evidence on pectin’s antidiarrheal effects in this population.

Several limitations should be acknowledged. First, no placebo was provided to patients assigned to the control group, which may introduce performance bias. A matched placebo was not feasible, as low-esterified pectin rapidly forms a visible and palpable gel via Ca^2+^-mediated crosslinking when mixed with enteral formula, and no biologically inert alternative can currently replicate this transformation. To address this potential bias, treating physicians responsible for nutritional therapy were independent of the study investigators and remained blinded to treatment allocation. Furthermore, both groups were managed under the same standardized CCCNTG feeding protocol to ensure uniform nutritional management, and all outcome assessments and statistical analyses were conducted by personnel blinded to treatment allocation.

Second, the control group receives usual nutritional care without a mandated fiber-free formula, which may introduce confounding if fiber-containing formulas are used. Given the limited use of fermentable soluble fiber in standard ICU enteral formulas across participating centers, the magnitude of this confounding effect is expected to be modest.

Third, the viscosity-enhancing properties of low-esterified pectin may compromise the reliability of gastric residual volume (GRV) measurement in the intervention group, as the viscoelastic gel formed in the gastric lumen can resist aspiration through a nasogastric tube, leading to systematic underestimation of true residual content. As our protocol does not mandate GRV-based EN management, consistent with current evidence and guideline recommendations, EN tolerance is assessed using functional clinical endpoints. The relationship between pectin-induced viscosity and gastric emptying in critically ill patients warrants further investigation.

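### Fixed blocks of 4 within site, in an open-label trial, let staff who know the block size and track earlier allocations deduce about one third of assignments before enrolment

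*Protocol article*

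**What the plan says.** Section 2.2 of the protocol article (Randomization and blinding) describes a computer-generated list "with a fixed block size of 4, ensuring allocation in a 1:1 ratio". It adds: "Randomization will be stratified by study site". Each site therefore works through its own run of blocks, each holding two pectin and two control assignments. The safeguard is stated as: "Allocation concealment will be ensured through a secure, encrypted, password-protected central web-based randomization system".

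The same section says: "Blinding of participants and treating clinicians was not feasible because pectin supplementation changes the handling and administration characteristics of the enteral formula". It also says: "No placebo will be provided to the control group". Section 2.3.1 has pectin given as separate boluses through the gastric tube. An assignment is therefore visible at the bedside once it has been made.

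The Discussion says something different about blinding: "treating physicians responsible for nutritional therapy were independent of the study investigators and remained blinded to treatment allocation".

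Section 2.1 plans 212 patients from ten ICUs, with recruitment from February 2024 and expected to end in 2026. No per-site numbers are given, and no varying or undisclosed block size is mentioned.

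**The concern.** Central randomization hides the list, but it cannot hide what the site has already seen. When the block length is fixed and known, the end of each block follows from its beginning. Site stratification means the relevant history is exactly the one that local staff can observe.

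This matters because several eligibility criteria in sections 2.1.1 and 2.1.2 rest on judgement. They include how long ventilation is likely to continue, whether gastric feeding is planned, whether early death is expected, and whether the clinician wants a special formula. A recruiter who can predict the next arm could approach or decline patients according to how well they are expected to tolerate feeding. Tolerance drives the primary outcome, the Day 5 ratio of enteral energy intake to target. The two-sample comparisons stated in section 2.7 are unadjusted, so they would not correct a resulting difference in prognosis.

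**Working it through.** **Inputs.** Block size 4, 1:1, within site (2.2). 212 patients over ten ICUs, 21.2 per site on average (2.1); an even spread is an assumption. Control mean 62.9%, SD 31.1%, relative increase 20%, 96 per arm (2.6).

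**The plan's own figure.** Target difference = 0.20 × 62.9 = 12.58 points. n per arm = 2 × (1.960 + 0.842)² × 31.1² / 12.58² ≈ 96, as stated. The sample size is not in question.

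**Deducible allocations, fixed blocks of 4.** A block has 6 equally likely orders. The next assignment is certain once one arm has been used twice. The chance of that at positions 1 to 4 is 0, 0, 1/3 and 1.
- Per block: 4/3 certain assignments of 4 = 33.3%.
- Site of 21: five complete blocks give 5 × 4/3 = 6.67, and the 21st patient adds none, so 6.67/21 = 31.7%.
- Whole trial (eight sites of 21, two of 22): 10 × 6.67 = 66.7 of 212 = 31.4%.

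**Best guess (the arm that is behind; a coin toss when level).** The chance of being right at positions 1 to 4 is 0.5, 0.667, 0.667 and 1.
- Per block: 2.833/4 = 70.8%.
- Site of 21: (5 × 2.833 + 0.5)/21 = 69.8%.

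**Undisclosed random blocks of 4, 6 and 8.** In simulated sites of 21 patients, the guesser knows which sizes are in use but not where blocks begin, and updates after each allocation. About 2.3% of allocations are certain and 66.8% of best guesses are right. A guesser who does not know the sizes cannot do better than this on average.

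**Larger fixed blocks help less.** Complete fixed blocks of 6 leave 25% certain, and blocks of 8 leave 20%.

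**Bias.** Suppose recruiters raise the mean ratio by δ points in patients they expect to get pectin and lower it by δ in those they expect to get control. δ is an assumption; nothing in the document gives it.
- Acting only on certain allocations (share c): bias = 2 × c × δ.
- Acting on every best guess (accuracy p): bias = 2 × (2p − 1) × δ.

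| At 21 patients per site | Multiplier of δ | δ = 2 | δ = 5 |
|---|---|---|---|
| Fixed 4, certain only | 2 × 0.317 = 0.63 | 1.3 | 3.2 |
| Fixed 4, every best guess | 2 × (2 × 0.698 − 1) = 0.79 | 1.6 | 4.0 |
| Random 4/6/8, certain only | 2 × 0.023 = 0.05 | 0.1 | 0.2 |
| Random 4/6/8, every best guess | 2 × (2 × 0.668 − 1) = 0.67 | 1.3 | 3.4 |

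**Power without the predictable third.** 96 × 2/3 = 64 per arm. The standard error rises from 31.1 × √(2/96) = 4.49 to 31.1 × √(2/64) = 5.50 points. Power for 12.58 points falls from 80% to about 63%.

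**The case against.** The strongest reply is that this is a possibility and not an observed fault. A reader might infer that staff already know a third of the assignments. The document does not support that: it does not say when sites learned the block size, or that anyone tracks allocations in order.

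The opportunity is also narrower than it first looks. Patients must have been in the ICU for less than 24 hours. With about 21 patients per site between February 2024 and some point in 2026, a site enrols roughly 0.6 to 0.9 patients a month. Holding a patient back changes the assignment only if someone else is enrolled there within those hours. Selective approach or refusal is the realistic route.

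A reader might also take the upper figure, about 4 points or a third of the target effect, as an estimate of bias. It is not. It needs δ = 5 and every recruiter acting on every best guess, including weak ones.

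Nor do varying blocks cure everything. Against a recruiter who plays every best guess, they lower the bias only from 0.79 to 0.67 of δ.

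These limits stand. The Discussion's blinding statement is a weaker defence. It conflicts with section 2.2, and it covers the physicians responsible for nutritional therapy, not everyone who enrols patients or gives the boluses. Finally, the statistical analysis plan is not shown and may already contain a predictability check, so its absence from section 2.7 is not a criticism.

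**Conclusion.** The point holds as a weakness in a stated design choice. Under fixed blocks of 4 within site, 33% of allocations in complete blocks, and about 32% at an assumed 21 patients per site, can be deduced by someone who knows the block size and has followed the site's earlier allocations. Central web-based randomization does not remove this.

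Whether anyone has used it, and how much bias would follow, cannot be read from the document. For an assumed δ of 2 to 5 points the bias is about 1.3 to 4.0 points against a target of 12.6, and it scales directly with δ. The change is worth making because it is cheap and removes nearly all certain knowledge. It does not show that the trial's result will be biased.

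**What to change.** 1. In section 2.2, for allocations not yet used, have the independent statistician regenerate each site's list from that site's next block boundary. Use randomly varying block sizes (for example 4, 6 and 8) that are not disclosed to sites. Patients completing a block already begun stay as predictable as before.
2. Because earlier patients are already enrolled, pre-specify a check, in section 2.7 or the statistical analysis plan if it is not already there. Compute for each patient the allocation probability implied by the site's earlier allocations, and examine whether baseline SOFA, APACHE II and mNUTRIC differ by it. All three are in Table 1, so no new data are needed.
3. Pre-specify a repeat of the primary analysis without the fully predictable allocations, as a sensitivity analysis only.
4. Reconcile the blinding statements in section 2.2 and the Discussion, and say who enrols patients and what they can see.

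The cost is a short amendment, a new list, a reload of the web system and a little more analysis. Within-site imbalance at the end of recruitment could be slightly larger. The sensitivity analysis has about 63% power at 64 per arm, so a non-significant result there should not be read as refuting the primary one. The gain from step 1 depends on how many patients remain to be enrolled, which the document does not give; steps 2 and 3 do not depend on it.

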#### ICU procedures common to both arms

2.3.3

Once randomized, the treating clinical team will determine the target infusion rate (mL/hour) for continuous EN to meet the energy requirement. Selection of the EN formula, estimation of protein needs, and blood glucose management will follow the CCCNTG feeding protocol or the standard procedures of each participating site.

Feeding intolerance will be managed according to the CCCNTG feeding protocol. Initial strategies include the use of prokinetic agents (e.g., erythromycin, metoclopramide) and adjustments to the EN formula. For patients with persistent gastric intolerance despite prokinetic therapy, postpyloric feeding will be implemented. If intolerance continues even after postpyloric feeding is attempted, PN will be commenced.

All patients will receive routine clinical care as determined by the local ICU team, including monitoring of vital signs, analgesia and sedation, fluid therapy, mechanical ventilation, renal replacement therapy, and vasoactive support. All cointerventions will be undertaken at the discretion of the treating clinicians and documented in the medical record.

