### Sample size estimation

2.6

Based on a previous nationwide multicenter trial (the NEED trial) conducted by the CCCNTG (19), among patients receiving invasive mechanical ventilation, the mean (standard deviation) ratio of EN energy intake to the prescribed target energy on Day 5 was 62.9% (31.1%) in the control group. Assuming a minimal clinically meaningful relative increase of 20% in the intervention group, with 80% power, a two-sided alpha of 0.05, and a 1:1 allocation ratio, the required sample size is 96 participants per arm (PASS ver.11.0; NCSS, LLC). To account for potential attrition, including withdrawal or dropped, estimated at approximately 10%, the final sample size was increased to 212 participants (106 per group).

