Statistical methods: Normality of continuous variables will be assessed using the Shapiro-Wilk test. Normally distributed continuous variables will be summarized as mean ± standard deviation and compared using Student’s *t*-test; non-normally distributed variables will be summarized as median (interquartile range, IQR) and compared using the Mann-Whitney U test. Categorical variables will be summarized as counts and percentages and compared using Pearson’s chi-square test. Effect estimates with 95% confidence intervals (CIs) will be reported throughout. No adjustment for multiple comparisons will be applied; all secondary outcome analyses are considered exploratory and hypothesis-generating. For secondary outcomes, complete-case analysis will be used, with missing data rates reported for each outcome. A two-sided *P*-value < 0.05 will be considered statistically significant.

Subgroup analyses: Pre-specified subgroup analyses will be conducted according to the following baseline characteristics: age (>60 vs. ≤59 years), BMI (>25 vs. ≤25 kg/m^2^), SOFA score (≥9 vs. <9), and ICU admission type (emergency, surgical, medical, or other).

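### Allocation is stratified by site but the fixed two-sample tests ignore site: conservative inference and some forgone precision, with the planned 80% power intact

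*Protocol article*

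**What the plan says.** Under Randomization and blinding the protocol article states: "Randomization will be stratified by study site". The sequence is generated "with a fixed block size of 4, ensuring allocation in a 1:1 ratio". Under Study design, setting, and population: "The trial will enroll 212 critically ill adult patients from ten intensive care units (ICUs) across China".

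Under Data analysis, the statistical methods paragraph sets one rule for all continuous variables. Those that pass a Shapiro-Wilk test are compared by Student's t-test; otherwise "non-normally distributed variables will be summarized as median (interquartile range, IQR) and compared using the Mann-Whitney U test". Categorical variables go to Pearson's chi-square test. The paragraph on the primary outcome deals with deaths and missing data and names no test, so the Day 5 ratio falls under this general rule. The time-to-event paragraph names a Fine-Gray model and a log-rank comparison without mentioning covariates or strata.

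The sample size section is a plain comparison of two means with no site term. The control mean and standard deviation (SD) "was 62.9% (31.1%) in the control group" come from an earlier multicenter trial.

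**The concern.** Stratified blocks hold the arms nearly balanced within each site, so differences between sites largely cancel out of the treatment difference. A two-sample test that ignores site still counts those differences in its standard error. The analysis therefore does not match the randomization, and the mismatch acts in one direction: intervals too wide, p-values too large, type I error below the nominal level.

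Site differences in the outcome are plausible. Formula choice, protein estimation and glucose control "will follow the CCCNTG feeding protocol or the standard procedures of each participating site", and co-interventions are left to the treating clinicians. At stake is the precision of the primary result, not its validity.

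**Working it through.** **Inputs from the protocol article.** Control mean 62.9%, SD 31.1%; "Assuming a minimal clinically meaningful relative increase of 20% in the intervention group", so the difference is d = 0.20 × 62.9 = 12.58 percentage points; two-sided alpha 0.05; power 80%; 96 per arm before attrition.

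**Assumptions.** (1) The SD of 31.1 is a total SD that includes variation between sites. (2) The share of variance between sites (the intraclass correlation, ICC) is not given, so a range from 0 to 0.20 is shown. (3) The formulas treat the arms as balanced within site. Incomplete blocks and exclusions before Day 5 loosen this slightly.

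**The plan's own figure.** n = 2 × [(1.960 + 0.842) × 31.1 / 12.58]² = 95.9, so 96 per arm. The stated figure is reproduced. The normal approximation gives 80.0% power at 96 per arm; the exact t-test gives 79.6%.

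**Effect of ignoring site.**
- Standard error used by the t-test: s0 = 31.1 × √(2/96) = 4.489, so d/s0 = 2.802.
- True standard error under site-stratified allocation: s1 = s0 × √(1 − ICC).
- True type I error of the unadjusted test: 2 × [1 − Φ(1.96/√(1 − ICC))].
- Power, unadjusted: Φ[(2.802 − 1.96)/√(1 − ICC)].
- Power, site-adjusted: Φ[2.802/√(1 − ICC) − 1.96].

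| Assumed ICC | Standard error too large by | True type I error | Power unadjusted | Power site-adjusted | n per arm for 80%, site-adjusted |
|---|---|---|---|---|---|
| 0 | 0% | 5.0% | 80.0% | 80.0% | 96 |
| 0.01 | 0.5% | 4.9% | 80.1% | 80.4% | 95 |
| 0.02 | 1.0% | 4.8% | 80.3% | 80.8% | 95 |
| 0.05 | 2.6% | 4.4% | 80.6% | 82.0% | 92 |
| 0.10 | 5.4% | 3.9% | 81.3% | 84.0% | 87 |
| 0.20 | 11.8% | 2.8% | 82.7% | 88.0% | 77 |

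**What the gain is worth at ICC 0.10.** For the unadjusted test to reach the 84.0% that adjustment gives, d/s0 must be 1.960 + 0.994 × 0.949 = 2.903. Then n = 2 × (2.903 × 31.1 / 12.58)² ≈ 103 per arm, and 103/96 = 1.07, or about 7% more patients.

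**Simulation check** (ten unequal sites, blocks of 4, 192 patients, normal data, 3,000 runs per setting):

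| ICC | t-test standard error: model / empirical | Type I error, t-test | Power: t-test | Power: Mann-Whitney | Power: site fixed effects |
|---|---|---|---|---|---|
| 0 | 4.48 / 4.47 | 5.3% | 80.0% | 78.0% | 79.7% |
| 0.05 | 4.47 / 4.36 | 4.5% | 79.3% | 77.4% | 80.5% |
| 0.10 | 4.45 / 4.27 | 4.5% | 81.4% | 78.8% | 84.0% |
| 0.20 | 4.41 / 4.04 | 3.3% | 82.5% | 80.0% | 87.5% |

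(Standard errors are from the runs with no treatment effect.) Simulation error on a power near 80% is √(0.8 × 0.2/3000) ≈ 0.7 points, so the 79.3% at ICC 0.05 is within noise of the exact t-test's 79.6% without site effects. The direction agrees with the formulas. The loss of type I error is somewhat milder than the formulas give.

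**The case against.** The strongest reply is that nothing the sponsor planned for is lost. The trial was sized without a site term, and the unadjusted t-test delivers that power or slightly more if sites differ. This stands. A reader might infer that power already paid for is wasted, or that the trial drops below 80%; the figures do not support either.

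Second, the size rests on an ICC that the documents do not give, and several features limit site differences: one weight-based energy target for all, intolerance managed under a common feeding protocol, and a statement in the Discussion that both arms share it. This also stands. An ICC of 0.10 to 0.20 is an assumption, and the point nearly vanishes below 0.02.

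Third, a reader might infer that every analysis in the plan ignores site. For the log-rank and Fine-Gray analyses the text is silent on strata and covariates, which a separate analysis plan may settle. The finding covers the tests that the article positively fixes.

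Two further readings go too far. Setting 87 against 96 per arm suggests a gain worth about 10% more patients at ICC 0.10, but it overlooks that the unadjusted test already has 81.3% there. The Mann-Whitney figures below 80% also do not show harm from ignoring site: the test has 78.0% in simulated normal data with no site effect at all, and the plan would use it only for data that fail the normality test.

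**Conclusion.** The mismatch is real and lies in the text itself: site is the stratification factor, and the tests that govern the primary outcome and the other simple comparisons cannot use it. The consequence is conservative inference, not bias and not an inflated type I error. Over an assumed ICC of 0.05 to 0.20 the primary standard error is 2.6 to 11.8% too large, and about 1 to 5 points of power are forgone relative to a site-adjusted analysis of the same patients. This rests on the SD being a total SD and on the assumed ICC. The figures apply to the t-test; no size was derived for the chi-square, log-rank or Fine-Gray analyses. The change is worth making because it costs almost nothing, not because the trial is underpowered without it.

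**What to change.** Before unblinding, define the primary analysis as a linear model of the Day 5 ratio on treatment and site (site as fixed effects or a random intercept). Report the adjusted mean difference with its 95% confidence interval, and keep the unadjusted test as supportive.

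For the secondary comparisons, use site-stratified versions where event numbers allow, for example Mantel-Haenszel for proportions. State explicitly whether the log-rank and Fine-Gray analyses are stratified by site. Further baseline covariates are optional and not part of this point.

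Site is already recorded for randomization, so no new data or patients are needed. Because the article itself names the tests, the change should be a dated amendment to the stated analysis as well as an analysis plan entry. With recruitment expected to finish in 2026 and analysts blinded, it can be made without knowledge of the results.
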